### Outcomes

The primary outcome of this study is to reduce musculoskeletal pain in the elderly. The secondary outcomes would be reduction in psychological distress (depression, anxiety, and stress) and improvements in beliefs among elderly using the health belief model constructs.

### Sample size

With a confidence level of 95% and a test power of 80%, the number of samples required for each group (intervention and control) is determined based on study conducted by Rostami et al. [42]. The required number of samples is estimated 55 per each group. Considering a 10% drop out, a sample of 60 participants per each group will be included.

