### Sampling

For sampling in the first stage, Tehran will be divided into four clusters of north, south, east, and west. A lottery method will be used to select nursing homes in each cluster, by assigning a number to each nursing home. The numbers will be written on a card, which will be placed in a container and thoroughly mixed. Two cards are then selected, one card representing the intervention group and the other representing the control group. The intervention and control groups (each consisting of 15 individuals) are selected from elderly homes according to the criteria for identification and selection. The reason for sampling from all four clusters is to generalize the results to the entire population.

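### The 80% power claim shows no allowance for allocating whole nursing homes, although the lottery described implies only four homes per arm

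*Protocol article*

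**What the plan says.** **Sample size.** The calculation is introduced with "With a confidence level of 95% and a test power of 80%, the number of samples required for each group" and attributed to a cited study. The result is "The required number of samples is estimated 55 per each group", followed by "Considering a 10% drop out, a sample of 60 participants per each group will be included". No effect size, SD, formula, ICC or design effect is given. Drop-out is the only stated step from 55 to 60.

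**Sampling.** "Tehran will be divided into four clusters of north, south, east, and west". Then: "A lottery method will be used to select nursing homes in each cluster, by assigning a number to each nursing home". The arms are set by the draw: "Two cards are then selected, one card representing the intervention group and the other representing the control group". On numbers: "The intervention and control groups (each consisting of 15 individuals) are selected from elderly homes according to the criteria for identification and selection".

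**Elsewhere.** Study setting speaks of one nursing home in the singular. Blinding says that people, not homes, are allocated by lottery. Recruitment and the Discussion refer to several homes or centres.

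**The concern.** If whole homes are allocated, residents of one home share staff, routines and (in the intervention arm) the same group sessions, so their pain scores are likely to be correlated. Sixty residents in four homes then carry less information than sixty independently allocated people. The comparison also rests on only eight allocated units, which limits the degrees of freedom of any test that respects the allocation.

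A figure of 55 per group with no visible cluster allowance therefore does not support 80% power under the allocation described. Power for pain, the primary outcome, would be overstated. A null result could be read as evidence of no benefit when the trial could reliably detect only a considerably larger difference.

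**Working it through.** **Inputs from the document.** 95% confidence, taken as two-sided 5% because sidedness is not stated; power 80%; 55 per group required, 60 enrolled, 10% drop-out (Sample size). Four areas, one home per arm per area, 15 residents per home (Sampling).

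**Assumptions.** ICC of 0.01, 0.05 or 0.10, because the document gives none. Equal numbers per home.

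**Step 1: the plan's own figure.** The 55 cannot be reproduced without an effect size and SD. It can be back-solved on the basis of individual allocation:

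- Normal approximation: d = √(2/55) × (1.960 + 0.842) = 0.1907 × 2.802 = 0.534.
- Two-sample t-test: d = 0.539, used below.

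**Step 2: homes per arm.** 4 areas × 1 home = 4 per arm, 8 in all. 4 × 15 = 60 per arm, which matches Sample size. With 55 evaluable per arm, m = 55/4 = 13.75 per home.

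**Step 3: design effect.** DE = 1 + (m − 1) × ICC = 1 + 12.75 × ICC. Effective number per arm = 55/DE. Standard error in SD units = √(2 × DE/55).

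**Step 4: power at d = 0.539.** Noncentral t with noncentrality 0.539/SE. The design-effect-only column uses the individual-level 108 df. The home-level column uses 2 × (4 − 1) = 6 df.

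| ICC | DE | Effective n per arm | SE | Noncentrality | Power, design effect only | Power, 6 df |
|---|---|---|---|---|---|---|
| 0 | 1.00 | 55 | 0.191 | 2.83 | 80% | 66% |
| 0.01 | 1.13 | 49 | 0.203 | 2.66 | 75% | 61% |
| 0.05 | 1.64 | 34 | 0.244 | 2.21 | 59% | 46% |
| 0.10 | 2.28 | 24 | 0.288 | 1.87 | 46% | 35% |

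**Step 5: detectable difference.** On 6 df, 80% power needs a noncentrality of about 3.37. Multiplying by the SE gives 0.68, 0.82 and 0.97 SD at ICC 0.01, 0.05 and 0.10, against the 0.54 implied by the plan.

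**Step 6: drop-out.** 60 × 0.9 = 54, one short of 55. To keep 55 after 10% loss requires 55/0.9 = 61.1, i.e. 62. With 54 per arm, power before any clustering is 79.3%.

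**The case against.** **The unit of allocation is not stated consistently.** Blinding refers to allocating people, Study setting to a single home, and the trial is called a parallel randomised trial, never a cluster trial. If individuals were randomised, the shortfall above would largely disappear. This stands as a reason to call four homes per arm an inference. It does not displace it: the Sampling section is the only procedure described, it assigns homes, and its arithmetic gives exactly the 60 per group.

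**The 55 might already contain an allowance.** With no formula shown, this cannot be strictly excluded. A reader might take it as established that 55 is an individual-level number, and the document does not go that far. What it shows is that no allowance is stated and that drop-out is the only visible inflation.

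**The size of the loss depends on assumptions.** This is fair. At ICC 0.01 the design effect alone costs about 5 points; the further fall to 61% comes from a 6-df home-level test, which the Data analysis section does not describe. Analysing individuals and ignoring homes would not rescue the claim, however: the nominal 5% error becomes about 6.5%, 13% and 19% at ICC 0.01, 0.05 and 0.10.

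**Baseline data could help.** The Data analysis section models change in pain and uses repeated measures. If the 55 came from raw post-intervention means (unknown) and the baseline correlation were 0.6 (assumed), 6-df power would be about 79%, 64% and 50%. Some power may be recovered, but the sample size statement claims no such gain.

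**Pairing by area.** It is tempting to treat the four areas as matched pairs and quote 3-df power of 45%, 34% and 26%. Those figures charge the full design effect and give pairing no credit. If pairing removed all between-home variance they would be about 49%, 51% and 53%. The lower set should not be quoted without that qualification.

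**Drop-out.** One resident per arm and less than one percentage point of power is close to rounding and carries no weight by itself.

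**Conclusion.** The point holds: the 80% claim is wrong as written, because it is not supported by the allocation the same document describes. An article may leave its full derivation to a longer document; the problem is that an explicit power figure conflicts with an explicit allocation procedure.

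The loss ranges from modest (75%, ICC 0.01, design effect only) to large (35%, ICC 0.10, home-level test). With four homes per arm, a 6-df test at the back-solved difference falls short even at ICC 0 unless power is recovered elsewhere. These sizes rest on three things the document does not state: that 55 was derived for individuals, the ICC, and the test used. A reader might infer that the trial has some definite lower power, such as 46% or 35%. The document does not support any single replacement figure, only the range under stated assumptions. The drop-out discrepancy is a minor correction.

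**What to change.** 1. Reconcile Study setting (one home) and Blinding (people allocated) with Sampling (homes drawn by lottery), so that the unit of allocation and the number of homes per arm are stated once and consistently.
2. If homes are the unit, replace the 80% claim with the power, or the detectable VAS difference, for 8 homes of 15 residents, over a stated ICC range (for example 0.01 to 0.10), with home-level degrees of freedom and 10% loss. Give the effect size and SD taken from the cited study so that the result can be read in VAS points.
3. If credit is taken for baseline adjustment or for pairing by area, state the assumed correlation or variance reduction. Any 3-df figure should say what gain from pairing it assumes.
4. In the same paragraph, correct the drop-out line: 10% loss from 60 leaves 54.

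The cost is a rewritten paragraph and consistent wording in two other sections. No additional participants are asked for. The downside is that the stated power becomes less favourable.

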### Recruitment

The necessary coordination will be done by the health education specialist with the relevant organizations. After obtaining permission from the nursing home, the health education specialist is responsible for explaining the objectives of the study to the nursing home officials and also obtaining informed consent from the elderly participating in the study. The intervention team works in cooperation with the main manager of the nursing home. Interventions will be carried out according to the program. All team members are present during the intervention period. After the end of the intervention time, one of the employees of each center will check the steps of the interventions and the adherence of the elderly to the interventions and send the relevant reports to the health education specialist on a weekly basis. The team doctor and health education specialist (principal investigator) will periodically meet with the elderly. Nursing homes that agree to participate in the project are included in the study. Potentially eligible seniors are enrolled in the study. In this study, the intervention team performs the training. The control group will receive the delayed intervention after completing the 6-month follow-up questionnaire.

### Sampling

For sampling in the first stage, Tehran will be divided into four clusters of north, south, east, and west. A lottery method will be used to select nursing homes in each cluster, by assigning a number to each nursing home. The numbers will be written on a card, which will be placed in a container and thoroughly mixed. Two cards are then selected, one card representing the intervention group and the other representing the control group. The intervention and control groups (each consisting of 15 individuals) are selected from elderly homes according to the criteria for identification and selection. The reason for sampling from all four clusters is to generalize the results to the entire population.

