### Who will take informed consent?

The necessary coordination will be done by the health education specialist with the relevant organizations. After obtaining permission from the nursing home, the health education specialist is responsible for explaining the objectives of the study to the nursing home officials and also obtaining informed consent from the elderly participating in the study.

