### Blinding

This study is not blinded. The main investigator is a health education specialist who manages the data. Allocation of people to intervention and control groups will be done randomly (lottery).

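### As described, a home's arm is set by the draw before its 15 residents are selected, with no stated safeguard on who is approached or who accepts

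*Protocol article*

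**What the plan says.** All references are to the Protocol article.

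- **Draw of homes (Sampling).** Tehran is divided into four areas. "A lottery method will be used to select nursing homes in each cluster, by assigning a number to each nursing home". Then: "Two cards are then selected, one card representing the intervention group and the other representing the control group".
- **Selection of residents (Sampling).** The sentence after the cards reads: "The intervention and control groups (each consisting of 15 individuals) are selected from elderly homes according to the criteria for identification and selection".
- **Consent (Who will take informed consent?, repeated in Recruitment).** "After obtaining permission from the nursing home, the health education specialist is responsible for explaining the objectives of the study to the nursing home officials". The same sentence gives this person the task for residents too: "also obtaining informed consent from the elderly participating in the study".
- **Role of that person.** Recruitment identifies the health education specialist as principal investigator: "The team doctor and health education specialist (principal investigator) will periodically meet with the elderly". The Intervention section lists the same role in the team that delivers the programme.
- **Blinding.** "This study is not blinded. The main investigator is a health education specialist who manages the data". The next sentence there says that it is people who are allocated to the groups by lottery.
- **Homes (Recruitment).** "Nursing homes that agree to participate in the project are included in the study".
- **Analysis (Data analysis).** A linear regression on change in pain, adjusted for gender and age group, with repeated-measures analysis of variance also planned.

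**The concern.** When whole homes are randomised, the lottery protects the comparison of homes. It protects the comparison of residents only if their identification and consent cannot depend on the arm. If the arm is known when residents are approached, two routes to imbalance open: the recruiter may approach different people in the two kinds of home, and residents may accept or decline according to what they are offered.

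Both routes are plausible here. The offers are very unequal, and the eligibility criteria leave room for judgement: musculoskeletal pain without a threshold, and ability to be physically active and to answer questions. The person taking consent is on the intervention team. The primary outcome is self-reported pain, which can depend on motivation, fitness and initial severity. A difference that enters at recruitment cannot be fully removed in the analysis, so it has to be prevented by the order of steps.

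**Working it through.** **1. Which scheme is operative.** Two homes in each of four areas, with 15 residents per home, give 4 × 15 = 60 per arm. The Sample size section also ends at 60 per group. It starts from 55 and allows 10% dropout: 55 × 1.10 = 60.5 (61 rounded up), or 55 / 0.90 = 61.1 (62 rounded up). The stated 60 is within two participants of either. The draw of homes in Sampling therefore fits the trial's own total. No step that allocates individual residents is described anywhere.

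**2. Order of steps, side by side.**

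| Step | Section | What is stated |
|---|---|---|
| Home drawn and arm set | Sampling | one act: each card stands for an arm |
| 15 residents per home selected | Sampling | described after the draw; selector not named |
| Consent of residents | Who will take informed consent?; Recruitment | after the home's permission; position relative to the draw not stated |
| Concealment of the arm | – | none described |
| Random or consecutive choice of the 15 | – | none described |

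**3. How unequal the offers are.** From the Intervention section:
- posture sessions: 8 weeks × 3 × 1 h = 24 h
- stress sessions: 8 weeks × 2 × 1.5 h = 24 h
- total: 48 h, before the vitamin D lecture, the belief-model sessions and the daily walking

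Control residents receive nothing until after the 6-month questionnaire.

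**4. What the planned analysis can absorb.** Pain is measured before the intervention and the regression models its change, so a difference in baseline pain level is partly dealt with. Regression to the mean is not, and neither gender nor age group stands in for motivation or fitness.

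**5. Illustration of size.** The documents give no figure for selective recruitment, so the shift *s* (in SD of the outcome) is an assumption. Further assumptions: no true effect, two-sided 5% test, independent residents, no adjustment. Then

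false-positive rate = 1 − Φ(1.96 − s/√(2/n)) + Φ(−1.96 − s/√(2/n)).

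For n = 60, √(2/60) = 0.1826. For s = 0.2, 0.2/0.1826 = 1.095, and the rate is 0.194 + 0.001 = 0.195.

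| Assumed shift (SD) | n = 60 per arm | n = 55 per arm |
|---|---|---|
| 0 | 5.0% | 5.0% |
| 0.1 | 8.5% | 8.2% |
| 0.2 | 19.5% | 18.2% |
| 0.3 | 37.6% | 35.0% |

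The rate rises with n: a larger sample does not cure a selection shift.

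**The case against.** The strongest reply is that the article does not state the timing. Consent is placed after the home's permission, not after allocation. The flowchart and the schedule of enrolment, which might show the order, are not reproduced in the text available. The Blinding section says people are allocated by lottery; if that were literally so, the mechanism above would not apply as written. This stands as a limit on certainty. It is not a defence, because the only procedure set out is the draw of homes, and the Blinding sentence conflicts with it.

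Several stronger readings are tempting and are not supported:

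- **That the investigator hand-picks the residents.** The documents name this person for explaining the study and taking consent. They do not say who chooses the 15.
- **That homes may refuse once they know their arm.** Recruitment says only that agreeing homes are included. Whether agreement comes before or after the draw is not stated.
- **That baseline pain is ignored.** Modelling change in pain addresses it in part. The exclusion of residents with mobility impairments or on pain medication also narrows the possible mix.
- **That a given share of the target effect could be due to selection.** The protocol states no effect size, test or sidedness. Back-solving from 55 per group at 80% power gives 0.534 SD if two-sided and 0.474 SD if one-sided, and any shift set against it would be a guess. Only an assumed range is defensible.

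**Conclusion.** The point holds for the procedure as described. The arm is fixed when the home is drawn, residents are selected from homes whose arm is already set, consent is taken by an unblinded member of the intervention team, and no safeguard is stated. This permits identification and recruitment bias, which the planned analysis would handle only in part.

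Two qualifications belong with it: consent after the draw is inferred from the order of the text, and the selector of residents is not named. Separately, and with no inference needed, Sampling (homes drawn) and Blinding (people allocated) contradict each other on the unit of allocation.

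A reader might conclude that the randomised comparison has no basis at all. That goes too far: homes are still drawn by lot, and harm arises only if recruitment in fact differs by arm. How much it would differ cannot be known from the documents. The false-positive rates of 8.5% to 37.6% for shifts of 0.1 to 0.3 SD show sensitivity under the listed assumptions and are not estimates for this trial. The conclusion rests on the order of steps and does not depend on them.

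**What to change.** Rewrite Sampling so that, within each area:

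1. two homes are drawn by lot and both agree to take part, before either arm is known;
2. all eligible residents in both homes are listed, and 15 are chosen by lot if more are eligible, taking the next on the random list when one declines;
3. consent is taken and the baseline questionnaires are completed in both homes;
4. only then is a card drawn to decide which of the two is the intervention home;
5. homes stay in their drawn arm in the analysis.

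State who lists and selects residents and what happens if fewer than 15 are eligible. Correct the Blinding section so that both sections name the same unit of allocation. If the order cannot be changed in some area, have a person unaware of the arm choose the residents by the same fixed rule; this is weaker, because residents' willingness to consent could still depend on the arm.

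**Cost.** No extra staff or participants, and no change to the sample-size figures. Both homes of a pair must finish baseline before the intervention home can start.

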### Blinding

This study is not blinded. The main investigator is a health education specialist who manages the data. Allocation of people to intervention and control groups will be done randomly (lottery).

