**Methods:**

This is a parallel randomized clinical trial among elderly people aged 60 years and over living in a nursing home who suffer from musculoskeletal pain. Eligible participants will be divided into two groups including the intervention group who will receive a multidisciplinary intervention (vitamin D consumption, psycho-social stress management, and physiotherapy) and the control group who will receive usual care. Data collection instruments will include demographic data, the Depression, Anxiety, and Stress Scale (DASS), the visual analogue scale (VAS), and a self-designed questionnaire containing the HBM constructs. The interventions will be carried out by the educational team (general practitioner, psychologist, physiotherapist, and health education specialist). Interventions include changing the wrong beliefs of the elderly, taking 800 units of vitamin D daily, daily walking exercise by the elderly for at least 30 min and maintaining proper body posture during daily activities, muscle relaxation, relaxation techniques, regular exercise, examining their diet and eliminating stimulants (such as smoking and coffee), regular visits with friends and family, and deep breathing techniques. All questionnaires will be completed by the elderly before, after, 3, and 6 months after the intervention.

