### Study setting

The study will be carried in a nursing home in Tehran, Iran. There is evidence that usually a sample of people living in Tehran would be a representative of Iranian population [36, 37].

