### Intervention

This is a multifaceted intervention to reduce the pain of the elderly by the intervention team (Table 2). The intervention team includes a general practitioner, psychologist, physiotherapist, and health education specialist.Physical activity would contain daily walking exercise by the elderly for at least 30 min and maintaining proper body posture during daily activities. Walking is done on a flat, un-sloped surface in their nursing home for half an hour. The proper posture of the body means a combination of the position of the different joints of the body relative to each other at the same time. The position of each joint will affect the position of the other joints. The proper posture is the position in which the least pressure is placed on the joints and the muscle activity is at its lowest level [38]. The proper posture involves proper position of the joints while standing, walking, sitting, and sleeping that will be laid in least stressed (to support muscles, joints, and ligaments during movement and activity). Sessions are held for 8 weeks, with three 1-h sessions per week, to maintain proper posture [39]. The training is done by the physiotherapist in the nursing home. First, how to maintain the correct body position and how to do it by the physiotherapist will be described, then he asks the elderly to perform the correct movements under the supervision of the physiotherapist to prevent injury. Films and posters are used for training as well as reminders.Vitamin D intake: A session will be given by the doctor in the form of a lecture about the benefits of vitamin D consumption for an hour. The doctor is obliged to answer the questions of the elderly. Each elderly person is given a daily dose of 600 to 800 IU of vitamin D tablets [40] for 6 months. One of the employees of the nursing home will be responsible for giving pills to the elderly daily. The doctor is obliged to answer the questions of the elderly during the intervention period.Psychological sessions will be conducted by a psychologist. Considering the conditions and facilities available, stress and depression reduction sessions should be carried out in such a way that all elderly people can benefit from them. These sessions include examining the elderly’s sleep, muscle relaxation, relaxation techniques, regular exercise, examining their diet and eliminating stimulants (such as smoking and coffee), regular visits with friends and family, and deep breathing techniques. These sessions are held by the psychologist for 8 weeks with 2 sessions per week, and each session lasts 90 min [41]. Training sessions in the nursing home will be conducted in the form of group discussions and proper training of techniques.Health belief model educational sessions will be held for changing the perceptions and beliefs of the elderly. After completing the self-designed questionnaire, training sessions are determined for each constructs. Training is done according to the type of constructs. Training sessions include group discussion, use of role models, increasing self-efficacy, etc. Meetings are held in the nursing home for 1 h, if the elderly wish, the meeting time can be extended. Considering that the model constructs target intervention behaviors in addition to the belief of the elderly, the presence of a health education specialist in other meetings is necessary.

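### The unit of allocation is stated in two incompatible ways: people in one nursing home, or whole homes in four areas of Tehran

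*Protocol article*

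**What the plan says.** The article describes who or what is allocated, and where, in several places.

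**Wording that points to people in one home**
- Study setting: "The study will be carried in a nursing home in Tehran, Iran".
- Abstract, Methods: the population lives in a nursing home (singular), and "Eligible participants will be divided into two groups".
- Blinding: "Allocation of people to intervention and control groups will be done randomly (lottery".

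**Wording that points to whole homes**
- Sampling: Tehran is split into four areas, then "A lottery method will be used to select nursing homes in each cluster, by assigning a number to each nursing home". Next, "Two cards are then selected, one card representing the intervention group and the other representing the control group". Finally, "The intervention and control groups (each consisting of 15 individuals) are selected from elderly homes".
- Recruitment: "Nursing homes that agree to participate in the project are included in the study".
- Table 2, Recruitment and the Discussion also refer to more than one centre.

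Trial design calls the study a parallel-group randomised trial and does not use the term cluster-randomised. In Sampling, the word cluster is used for the four areas of the city, not for the homes. Sample size gives 55 per group at 95% confidence and 80% power, raised to 60 for 10% dropout. Data analysis lists paired t-tests, comparison of independent group means, linear regression adjusted for gender and age group, and repeated-measures ANOVA. Neither section mentions the home.

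**The concern.** The unit of randomisation is a core design fact. If people are allocated within one home, the resident is the unit, and a sample size and analysis based on independent individuals can be judged on those terms. If homes are allocated, there are eight units, residents of the same home tend to resemble one another, and every resident of a home receives the same arm. The 80% power and the listed tests mean different things under the two designs. The trial can also make different claims about how it was randomised. A reader cannot tell from this article which design the sample size and analysis were meant to serve.

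There is a secondary, conditional issue. Sessions, films, posters and staff reminders are delivered inside the home. If both arms lived in one home, controls could be exposed to them.

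**Working it through.** **1. Which description fits the rest of the article?**

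Two homes in each of four areas gives 8 homes, 4 per arm. With 15 residents from each, 4 × 15 = 60 per arm, which is the figure in Sample size. Sampling is also the only section that gives an operational procedure. Home-level allocation is therefore the better-supported reading. The Abstract, Study setting and Blinding still contradict it as written.

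**2. The plan's own sample size**

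The 55 cannot be reproduced forward, because the article gives no effect size or standard deviation and refers only to a cited study. Back-solving with two-sided alpha 0.05 (an assumption, as sidedness is not stated) and 80% power:

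d = (1.960 + 0.842) × √(2/55) = 0.534

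This standardised difference is implied by the 55; the document does not state it. Dropout of 10% from 60 leaves 60 × 0.9 = 54 per arm, or 54/4 = 13.5 per home. With independent residents, d = 0.534 gives 83% power at 60 analysed per arm and 79% at 54.

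**3. Power if homes are allocated**

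Design effect: DEFF = 1 + (m − 1) × ICC. Effective n = 4m/DEFF. Power = Φ(0.534 × √(effective n/2) − 1.960). The ICC is not in the document, so the values below are assumed.

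| ICC (assumed) | DEFF, m = 15 | Effective n per arm | Power, 60 analysed | Power, 54 analysed (m = 13.5) |
|---|---|---|---|---|
| 0.01 | 1.14 | 52.6 | 78% | 74% |
| 0.02 | 1.28 | 46.9 | 73% | 70% |
| 0.05 | 1.70 | 35.3 | 61% | 59% |
| 0.10 | 2.40 | 25.0 | 47% | 46% |

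These use a normal approximation. With eight homes, a home-level comparison has about 6 degrees of freedom. Using the noncentral t with noncentrality 0.534/√(2 × DEFF/54):

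- ICC 0: 0.534/√(2/54) = 2.78, power 64%
- ICC 0.01 (DEFF 1.125): 0.534/√(2.25/54) = 2.62, power 59%
- ICC 0.05 (DEFF 1.625): 0.534/√(3.25/54) = 2.18, power 45%

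**4. Size needed to keep 80% (normal approximation, m = 15)**

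55 × 1.14 = 62.7, so 63 analysed per arm at ICC 0.01. 55 × 1.70 = 93.5, so 94 at ICC 0.05. The plan enrols 60.

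**The case against.** The strongest reply is that this is loose wording. Study setting says nothing about allocation, and Blinding says nothing about a single home. The lottery named in Blinding most naturally refers to the card draw described just before it, in Sampling, and people do enter an arm through their home. The plural homes and centres elsewhere, and 4 × 15 = 60, support this. As an account of the likely intent, that stands, and it is why the correction should run towards Sampling. It does not remove the contradiction. Trial design, Sample size and Data analysis all read as if individuals were allocated, so the wording in Blinding is not isolated. A condensed article may leave detail to a fuller document, but that does not excuse stating the unit of randomisation two ways.

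A reader might go further and infer that contamination will dilute the pain effect. If a share c of the benefit reached controls, power would be Φ(2.802 × (1 − c) − 1.960), or 71%, 61% and 50% at c = 0.1, 0.2 and 0.3. The documents do not support that as a headline:

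- It applies only if both arms share a home, which is the less likely reading.
- No value of c can be taken from the article.
- The instruction that "stress and depression reduction sessions should be carried out in such a way that all elderly people can benefit from them" follows a remark about available facilities and probably concerns those attending.
- Staff reminders are directed at the intervention group, and controls are to receive no intervention during the study.
- Vitamin D tablets are handed to each person, so a single c for the whole package fits poorly.

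**Conclusion.** The contradiction holds and is more than clerical. The Abstract and Study setting describe one home and Blinding allocates people, while Sampling allocates eight homes. On the better-supported reading the trial is cluster-randomised with four homes per arm, and the stated 80% power is less favourable than it looks. It is about 78% to 61% for an assumed ICC of 0.01 to 0.05 with all 60 per arm analysed, and about 59% to 45% with 54 analysed and 6 degrees of freedom. These figures illustrate the scale. They rest on the back-solved d of 0.534, a two-sided 5% test and an assumed ICC. A fuller protocol or analysis plan may account for homes; what is established here is that the article's statements do not fit one design. Contamination remains a secondary, conditional concern of unknown size.

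**What to change.** - **Abstract, Study setting, Blinding:** amend to match Sampling. State eight homes, one intervention and one control home in each of four areas, with the home as the unit of allocation and no home containing both arms.
- **Trial design:** call the trial cluster-randomised.
- **Intervention and adherence sections:** state that films, posters, group sessions and staff reminders are confined to intervention homes until the control homes have completed the 6-month questionnaire. This agrees with the delayed control intervention already in Recruitment.
- **Sample size:** restate power with a design effect for 15 residents per home, giving the assumed effect size and ICC.
- **Data analysis:** account for home in the comparison of arms, by a method suited to eight homes.

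The first three items cost only protocol wording if Sampling is the intended design. The last two have a real downside: the stated power will fall, and keeping 80% would probably need more homes. If allocation of individuals within one home was intended instead, Sampling, Recruitment, Table 2 and the Discussion must change, and contamination would then have to be addressed directly.
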